## Methods/design

The VF-HT-AF study is designed as a prospective, randomized, open-label, four-arm parallel, and multicenter study. The objective of the study is to test the hypothesis that upstream therapy using valsartan or fluvastatin is more effective in reducing the recurrence of AF and the progress from non-permanent AF to permanent AF in hypertensive patients with non-permanent AF, compared with conventional antihypertensive therapy using dihydropyridine calcium channel blockers (CCBs). This study will be conducted according to the principles outlined in the Declaration of Helsinki. Written informed consent will be obtained from all patients prior to the study. The study protocol has been approved by the ethics committee of the Second Hospital of Tianjin Medical University (Clinical ethical review, 2012, No. 27) as well as other participating medical centers, which are secondary or tertiary healthcare providers in China, and should provide proof of laboratory quality control. The ethical bodies that approved our study in the various centers are listed in Additional file 1. If there is any amendment to the protocol, approval must again be sought from the ethics committee. The study is registered with the Chinese Clinical Trial Registry (ChiCTR-TRC-12002642). The protocol design is based on the Consolidated Standards of Reporting Trials (CONSORT) and Standard Protocol Items: Recommendations for Interventional Trials (SPIRIT, see Additional file 2), and study results will be reported according to these guidelines.

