### Study design

The VF-HT-AF study is a randomized, multicenter, open-label, and four-arm parallel study to evaluate the effectiveness of valsartan, fluvastatin or a combination of both on recurrent AF in hypertensive patients with non-permanent AF in China. After providing informed consent, patients will be randomly assigned using a computer system to one of four groups (the valsartan group, the fluvastatin plus dihydropyridine CCBs group, the valsartan plus fluvastatin group, and the dihydropyridine CCBs group) by the School of Public Health of Tianjin Medical University, initially in a 1:1:1:1 ratio. Physicians, who should be qualified medical practitioners, screen and follow up the patients in hospital outpatient or inpatient clinics. All patients’ data will be collected using a standard case report form and transmitted to the central database at the data center. All centers will be regularly monitored for source data documentation. Missing or questionable data will be completed and corrected by queries.

If the candidate patients have not taken ARBs, ACEIs or statins in the past at least 14 days, they will be directly enrolled and randomized. If the candidate patients have taken ARBs, ACEIs or statins, they will be randomized after a 14-day washout period. Baseline data will be collected after the washout period.

The initial dose of fluvastatin will be 40 mg/day at night, while valsartan will be prescribed initially at 80 mg/day. The fluvastatin dose will be no less than 40 mg/day and that of valsartan will be no less than 80 mg/day during the follow-up period. Blood pressures in each group must reach the target blood pressure, which is set at <140/90 mm Hg.

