### Primary outcome measures

The VF-HT-AF study will examine whether fluvastatin or valsartan has anti-arrhythmic effects on non-permanent AF, apart from their lipid-lowering and antihypertensive effects, in comparison with dihydropyridine CCBs. Also, it will confirm whether a combination of valsartan and fluvastatin has better effects on non-permanent AF than either drug alone.

Therefore, the primary outcome measure is the change in the development of paroxysmal AF into persistent or permanent AF, the development of persistent AF to permanent AF, as well as the change in incidence of overall and persistent AF recurrence, which will be evaluated by 7-day Holter monitoring and patients’ diaries during the 2-year’s follow-up of the four treatment groups.

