### Statistical analysis

All analyses will be performed based on the intention-to-treat principle with differences assumed to be significant at a two-sided *P* value < 0.05.

Baseline characteristics and follow-up information will be collected for each group through the questionnaire. Absolute values for each question will be used to calculate the mean value, standard deviation, median value, percentile, number of cases, and percentages per group. Statistical significance will be evaluated by analysis of variance or Kruskal–Wallis rank sum test for continuous variables and chi-squared test for categorical variables, respectively. Kaplan–Meier curves will be used to describe the time-dependent occurrence of events, and the log-rank test will be performed to compare survival distributions for the four groups. To adjust for possible baseline imbalances between groups, a Cox proportional hazards model will be used. A hazard ratio will be calculated. In addition, subgroup analyses will be performed corresponding to the nature of the data. All statistical analyses will be performed using SPSS statistical software (version 17.00, Chicago, IL, USA).

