### Expected implications

The VF-HT-AF study will determine the anti-arrhythmic effects of the ARB and statin on the recurrence of non-permanent AF associated with hypertension. It will also examine the mortality, morbidity, and perpetuation of the arrhythmia under valsartan, fluvastatin, dihydropiridine CCBs or combined treatment.

In particular, prevention of persistent and permanent AF would be expected to reduce hospitalization for heart failure, the incidence of stroke, morbidity, and mortality in patients with hypertension. This study will provide data to health care policymakers and the authors of clinical guidelines regarding the appropriate use of upstream therapy in hypertensive patients with AF and provide directions for future research.

Therefore, the results of this study will emphasize the role of upstream therapies in the prevention of AF in a Chinese hypertensive population and assist in the design of an optimal therapy for such patients.

However, one important limitation that might be present in this study is that it is an open-label trial, because we do not have enough funds to make the drugs in blinded versions. The drugs that the patients will use in our study are all provided in hospitals or pharmacies. The patients and doctors will know the drugs used. Another limitation is that the control group is not blank, so we do not test the fluvastatin effect alone. Because the patients in our study are hypertensive patients, they must, for ethical reasons, be treated with antihypertensive therapy. We chose the group receiving dihydropyridine CCBs as the control group, comparing them with the dihydropyridine CCBs plus fluvastatin group. If the recurrence of AF in the dihydropyridine CCBs plus fluvastatin group is less than the dihydropyridine CCBs group, it will be proved that fluvastatin can reduce the probability of non-permanent AF in patients with hypertension. There may be some combined effects of dihydropyridine CCBs plus fluvastatin, but we have to use antihypertensive drugs.

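### The arms form a 2x2 layout with drug-specific hypotheses, but the only time-to-event test named is a four-group log-rank, which supports no single drug claim

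*Protocol article*

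**What the plan says.** The Study design section of the protocol article describes a "randomized, multicenter, open-label, and four-arm parallel study". Its arms are "the valsartan group, the fluvastatin plus dihydropyridine CCBs group, the valsartan plus fluvastatin group, and the dihydropyridine CCBs group", allocated "initially in a 1:1:1:1 ratio".

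The hypotheses are specific to the drugs. Methods/design states that "upstream therapy using valsartan or fluvastatin is more effective in reducing the recurrence of AF" (and in slowing progression to permanent AF) than CCB-based therapy. Primary outcome measures adds that "it will confirm whether a combination of valsartan and fluvastatin has better effects on non-permanent AF than either drug alone".

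The Statistical analysis section sets a two-sided 0.05 level. For time to event it plans Kaplan–Meier curves, and "the log-rank test will be performed to compare survival distributions for the four groups". A Cox model follows. Its stated purpose is to adjust for baseline imbalance, and it yields a hazard ratio (singular) with no contrast named.

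Sample size calculation rests on one contrast, valsartan against CCB, with a 6.8% lower incidence and 1404 patients before losses. It gives no control rate.

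Expected implications infers a fluvastatin effect from CCB plus fluvastatin against CCB. It lists as a limitation that the control group is not untreated, "so we do not test the fluvastatin effect alone".

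**The concern.** The four arms are the complete crossing of base drug (valsartan or CCB) with fluvastatin (yes or no). The questions concern particular cells and margins of that table. A log-rank test across four groups has 3 degrees of freedom, and its null hypothesis is that all four curves coincide. Rejecting it does not say which arms differ or in which direction.

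Two things are at stake. First, a positive headline test could be read as support for a drug that does nothing, and the contrast carrying the claim could be chosen after the four curves are seen. Second, the Discussion's rule for fluvastatin leaves out the randomised comparison of valsartan plus fluvastatin against valsartan, which bears on the same question.

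**Working it through.** **Layout.**

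| | No fluvastatin | Fluvastatin |
|---|---|---|
| CCB | CCB | CCB+F |
| Valsartan | V | V+F |

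Fluvastatin is compared within both rows, and valsartan against CCB within both columns.

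**Inputs.** From the article: 1404 patients and four equal arms, so 1404/4 = 351 per arm and 702 per factor level; a difference of 6.8%, read as absolute (0.068); two-sided alpha 0.05. Assumed: the control rate, which is not given.

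**The plan's own figure.** 1404 cannot be rebuilt without a control rate. For one two-sided pairwise test at 80% power, n per arm = [1.96√(2p̄(1−p̄)) + 0.8416√(p1(1−p1)+p2(1−p2))]²/(p1−p2)². With 15.2% and 8.4%, p̄ = 0.118 and n = (0.8942 + 0.3818)²/0.004624 = 352.1, against 351. So 15.2% is a rate that fits a pairwise reading. The figure also fits 702 per side at a control rate of about 31% to 34%, so the fit proves nothing about the intended analysis.

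**Formulas.** I used a binary event at end of follow-up as a stand-in for the log-rank.
- Two groups: power = Φ{[|p1−p2| − 1.96√(2p̄(1−p̄)/n)] / √([p1(1−p1)+p2(1−p2)]/n)}.
- Four groups: λ = nΣ(pi−p̄)²/[p̄(1−p̄)], referred to a noncentral chi-square on 3 df with critical value 7.815.

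**Only fluvastatin works (CCB and V at 15.2%; CCB+F and V+F at 8.4%).**
- Four-group: λ = 351 × 4 × 0.034²/(0.118 × 0.882) = 15.59, power 93%.
- CCB+F against CCB (n = 351): (0.068 − 0.0477)/0.0242 = 0.84, power 80%.
- Fluvastatin factor (n = 702): (0.068 − 0.03375)/0.01712 = 2.00, power 98% (96% at alpha 0.025).

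Simulating the four arms gave 93%, 80% and 98%. By symmetry the same figures apply if only valsartan works.

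**Range over the assumed control rate (difference 0.068, one drug active).**

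| Control rate | Two-arm | Four-group | Factor |
|---|---|---|---|
| 10% | 95.4% | 99.5% | 99.9% |
| 15% | 80.5% | 93.1% | 97.9% |
| 20% | 67.8% | 83.1% | 92.9% |
| 25% | 59.1% | 74.1% | 87.3% |
| 30% | 53.1% | 67.3% | 82.3% |

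**A smaller effect, from figures in the Discussion.** Progression of 5.5% per year over two years gives 1 − 0.945² = 10.7%. The quoted hazard ratio of 0.683 gives 1 − 0.893^0.683 = 7.4%. Power is 32% two-arm, 40% four-group and 57% factor.

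**On the event scale (Schoenfeld).** With the number of events that gives the factor test 80% power, the four-group log-rank has about 65% and a two-arm comparison about 51%. The required noncentrality is 10.90 for 3 df and 7.85 for 1 df, a ratio of 1.39.

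**Both drugs work with multiplicative risks (15.2%, 8.4%, 8.4%, and 8.4² / 15.2 = 4.6%).** The factor comparison is 11.8% against 6.5% and has power 93%. V+F against either single-drug arm has power about 53%.

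**Sub-additive case (CCB 15.2%, all other arms 8.4%).** The factor comparison is 11.8% against 8.4%: (0.034 − 0.0315)/0.01606 = 0.15, power 56% (45% at alpha 0.025). Pairwise against CCB stays at 80%. The four-group test has about 85% by simulation.

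**The case against.** Several points on the other side are sound.

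- A reader might infer that the planned log-rank throws away half the information on each drug. It does not, because it uses every arm. Its cost against a factor test is two extra degrees of freedom, or 1.39 times the events. The loss of half the patients belongs only to a two-arm contrast such as the one in Expected implications.
- A reader might infer that the plan answers none of its questions. That goes too far. A Cox model could carry every contrast, the Discussion names one for fluvastatin, and a full protocol or SAP that is not shown may list the rest. What remains is what the article does state: an omnibus test as its only named time-to-event comparison, and a single hazard ratio in a four-arm trial.
- A reader might take the remark about fluvastatin alone as an error. It is correct: no arm receives fluvastatin without valsartan or a CCB, and a factorial analysis does not change that.
- A factor analysis is not better in every case. The hypotheses in Methods/design and Primary outcome measures can be read as simple effects, and the combination question cannot be answered at the margins. The Discussion also says statins may act on the renin-angiotensin system, which is valsartan's target, so sub-additivity is plausible. In the case worked above, the factor test is the weakest of the three.

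These points limit the remedy. They do not make the four-group test an answer to a drug-specific hypothesis.

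**Conclusion.** The concern holds in this limited form. The design is a complete 2x2 with drug-specific hypotheses, and the one named time-to-event test cannot support any of them by itself. Under the assumed 15.2% and 8.4%, it is positive about 93% of the time when one of the two drugs is inert.

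The Discussion's fluvastatin rule uses half the randomised patients. Using all four arms raises power from about 80% to 98%, provided there is no interaction and the other drug has no effect. If both drugs act multiplicatively it is about 93%; if the effects are fully sub-additive it falls to about 56%. All these figures rest on assumed control rates and on a binary approximation to the log-rank. The ordering two-arm, four-group, factor holds across control rates of 10% to 30% when one drug is active and there is no interaction.

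The combination claim is the least protected. Under the multiplicative assumption each of its two contrasts has about 53% power, while the sample size section considers only valsartan against CCB.

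**What to change.** In Statistical analysis:
- Make the four-group log-rank and the Kaplan–Meier curves descriptive.
- Fit a Cox model with a valsartan factor (V and V+F against CCB and CCB+F) and a fluvastatin factor (CCB+F and V+F against CCB and V). Report each factor hazard ratio and the interaction hazard ratio with confidence intervals.
- Report the four simple effects: V vs CCB, CCB+F vs CCB, V+F vs V, and V+F vs CCB+F. Name the last two as the test of the combination hypothesis, give them a place in the testing order, and say whether both must succeed.
- State an alpha rule, for example 0.025 for each drug.
- Say that the valsartan factor is a substitution for CCB, not an addition to it.

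In Expected implications, keep the limitation that fluvastatin is not tested without a background antihypertensive. Add that its effect is estimated on both the CCB and the valsartan background.

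The cost is wording only, with no extra patients. The article reports that recruitment is under way, so the change can be made before the data are analysed. The drawback is that factor effects average over the other drug and lose power under sub-additive interaction, so the interaction and simple effects must be shown beside them.

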### Follow-up

Clinical follow-up using standardized questionnaires will be performed every 3 months during the 2 years follow-up period from the assignment of each patient.

The dosages and types of all other anti-hypertensive, anti-hyperlipidemia, and anti-arrhythmic drugs used during the follow-up will be recorded for each patient. Ultrasound echocardiography will be performed before the patients enter the study and at the end of the follow-up period. 7-day Holter monitoring will be performed at the baseline, 6 month, 12 month and at the end of the follow-up period. Patients’ diaries, cardiac function (NYHA classification) and adverse events during the follow-up period will be collected every 3 months.

Throughout the study, patients should record diaries when they feel discomfort. Arrhythmia-related symptoms are self-evaluated or evaluated by 7-day Holter monitoring, which has five poles, is weighted 50 g, 2.0 × 2.7 cm, and can record ECG for 7 days. The 7-day Holter instruments were manufactured by BORSAM Co. in Shenzhen, Guangdong Province, China, and provided by the study’s sponsor, Tianjin Institute of Cardiology, Tianjin, China. The attending physicians will also record blood pressure and ECG during each follow-up. Unless necessary, anti-arrhythmic drug therapy will be discontinued during the study according to the attending physicians’ advice for each patient. The design of the study is shown in Fig. 1.

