### Sample size calculation

The primary outcome measure is the change in the development of paroxysmal AF into persistent or permanent AF, the development of persistent AF to permanent AF, as well as the change in incidence of overall and persistent AF recurrence. Power calculations to provide estimates for the necessary sample size were conducted concerning the primary outcome measure. The sample size was estimated based on findings from the 12-month results of the J-RHYTHM II study [11], in which the incidence of persistent AF is estimated to be 6.8 % lower in the valsartan group than in the CCBs group. To ensure 80 % power at the 5 % significance level, a sample size of at least 1404 needs to be included. Considering a rejection rate of 20 %, about 1879 patients need to be approached.

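### Stratifying the primary log-rank and Cox models by AF type at entry would be a free gain in efficiency; the plan names no stratum and justifies adjustment only by possible imbalance

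*Protocol article*

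**What the plan says.** Under Statistical analysis, event times are described by Kaplan–Meier curves and the four groups are compared with a log-rank test. No stratum is mentioned. A Cox model follows, and its only stated purpose is this: "To adjust for possible baseline imbalances between groups, a Cox proportional hazards model will be used". No covariate is named, and AF type does not appear in that section.

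Under Patient population and entry criteria, non-permanent AF is eligible, and persistent AF is excluded only from a duration of one year. Both paroxysmal and shorter persistent AF therefore enter. Under Study design, allocation is "initially in a 1:1:1:1 ratio", with no stratification factor named.

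Under Primary outcome measures, the progression part reads "the change in the development of paroxysmal AF into persistent or permanent AF, the development of persistent AF to permanent AF". The other part, overall and persistent AF recurrence, applies to both entry types.

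**The concern.** Entry type is built into the progression endpoint. By the Definitions section, persistent AF lasts beyond 7 days, or lasts between 48 hours and 7 days with a decision to cardiovert. Permanent AF lasts more than a year, or follows a decision to give up on sinus rhythm. An eight-day episode is therefore progression for a patient who entered with paroxysmal AF, and is not for one who entered with persistent AF. The two types can be expected to have different progression rates, in a direction the article does not settle.

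When a baseline factor with this much influence is left out of a log-rank test or Cox model, the estimated hazard ratio moves towards 1 and power falls. Adjusting for possible imbalance does not address this, because the loss occurs even when the arms are perfectly balanced on AF type. A covariate belongs in the model because it predicts outcome, not because it happens to differ between arms.

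**Working it through.** **Plan's own figure.** The Sample size calculation section states "a sample size of at least 1404 needs to be included", that is 1404/4 = 351 per arm, for 80 % power at 5 %, because "the incidence of persistent AF is estimated to be 6.8 % lower in the valsartan group than in the CCBs group". No control rate is given, so 1404 cannot be derived from the stated inputs. The usual two-proportion formula, n = [1.96·√(2p̄q̄) + 0.84·√(p₁q₁ + p₂q₂)]²/0.068², gives 347 per arm at an assumed control rate of 15 % (15 % against 8.2 %), so 351 fits a control rate of about 15 %. This does not decide the present point; 351 per arm is used below.

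**Other inputs.** Two-sided 5 % level and two-year follow-up (stated). The only background rate given is 5.5 % a year for progression of paroxysmal AF (Discussion), which is 1 − 0.945² = 10.7 % over two years. Rates for persistent AF, the mix of types and the hazard ratio are not given. They are assumed below and varied.

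**Method.** Two arms, exponential event times within each AF type, and the same hazard ratio in both types. For either test, Z = U/√V, where U = ∫(d₁ − f·d)dt and V = ∫d·f(1 − f)dt. Here d₁ is the expected event rate in the treated arm, d the total event rate, and f the treated share of those at risk. The stratified test forms U and V within each type and sums them; the unstratified test pools first. Power ≈ Φ(|Z| − 1.96).

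**Worked case:** 70 % paroxysmal, two-year control rates 11 % (paroxysmal) and 50 % (persistent), hazard ratio 0.612.

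- Stratified: U = −16.12, V = 33.13, |Z| = 16.12/√33.13 = 2.80, power Φ(0.84) = 80 %. One-step hazard ratio exp(−16.12/33.13) = 0.615.
- Unstratified: U = −14.72, V = 33.23, |Z| = 14.72/√33.23 = 2.55, power Φ(0.59) = 72 %. One-step hazard ratio exp(−14.72/33.23) = 0.642.

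V hardly changes, so stratifying costs almost no information. The loss comes from U, which shrinks by 1 − 14.72/16.12 = 9 %.

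**Range.** Unstratified power, with the hazard ratio set in each cell so that the stratified test has 80 %:

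| Control rate, paroxysmal / persistent | 50 % paroxysmal | 70 % | 85 % |
|---|---|---|---|
| 11 % / 11 % | 80 % | 80 % | 80 % |
| 11 % / 25 % | 79 % | 79 % | 79 % |
| 25 % / 5 % | 77 % | 78 % | 79 % |
| 20 % / 50 % | 76 % | 76 % | 77 % |
| 11 % / 50 % | 73 % | 72 % | 74 % |
| 30 % / 80 % | 66 % | 67 % | 72 % |

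**Progression at 10 % / 30 %,** hazard ratio 0.53, 70 % paroxysmal:

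- Stratified: |Z| = 13.56/√21.88 = 2.90, power 83 %.
- Unstratified: |Z| = 13.21/√21.90 = 2.82, power 81 %.

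Simulation of the same case (2000 runs) gave 83.8 % and 81.4 %.

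**Type I error.** Over three null scenarios (6000 runs each), the unstratified test rejected in 5.0 % to 5.4 % of runs. Monte Carlo standard error is √(0.05 × 0.95/6000) = 0.3 points. Stratifying only when AF type was imbalanced at p < 0.05 gave 4.7 % and 4.8 % (8000 runs each). Only reporting whichever test was significant raised the error, to 6.3 % to 6.9 %.

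**The case against.** The strongest reply is that this rests on silence. A journal article condenses the plan, and strata and covariate lists are commonly left to an analysis plan, which is not shown. That stands as far as it goes: the article does not say that the log-rank is unstratified or that AF type will be ignored, and the missing covariate list is not the point. What remains is what the article does state. It gives imbalance as the sole reason for the Cox model, and an endpoint whose progression threshold depends on entry type.

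Several stronger readings are tempting, and the article does not support them.

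- A reader might infer that baseline tests will select the covariates. The article plans the Cox model outright and never links it to the ANOVA or chi-squared comparisons.
- A reader might infer an inflated error rate. The simulations show inflation only if the more favourable result is picked, which the article does not say will happen.
- A reader might infer that chance imbalance in AF type biases the primary test. With 30 % persistent, the 95 % range of the difference between two arms is 1.96 × √(2 × 0.3 × 0.7/351) = ±6.8 points, but this is ordinary randomisation variation already covered by the test's sampling error.
- A reader might infer that the two types have wholly different primary events. Recurrence is shared; only progression differs.

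It is also fair that the large power losses need extreme rates, such as 30 % against 80 %. For progression, moderate differences cost 1 to 3 points.

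**Conclusion.** The point holds as a free improvement. The stated reason for adjustment is a weak one in a randomised trial, and the plan as described makes no commitment to a factor that its own endpoint definition singles out. The cost of leaving AF type out is 0 to about 14 points of power, and about 2 points for progression at 10 % / 30 %, with some attenuation of the hazard ratio (0.615 to 0.642 in the worked case).

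These sizes rest on assumed event rates by AF type, an assumed mix of types, a common hazard ratio within types, and a two-arm comparison at 351 per arm. The article fixes only the number of patients, the significance level, the follow-up and one background rate for paroxysmal AF. The unstratified test would remain valid at about 5 %, so nothing here is a correction of bias.

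**What to change.** In the Statistical analysis section, replace the sentence on the Cox model with wording to this effect: the primary log-rank test and Cox model are stratified by AF type at entry (paroxysmal or persistent); any further covariates are fixed in advance because they predict outcome, and are used whatever the observed balance.

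The cost is wording only. Entry type must already be known to decide whether a patient has progressed, so no new data are needed. Randomisation and sample size need not change. If event rates turn out not to differ by type, the stratified test loses essentially nothing (first row of the table). Because the trial is open-label and was recruiting when the article was written, the change should be recorded before outcomes are compared by group.
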